### Inclusion criteria

In the study, we will recruit patients who have the following criteria: (1) patients with colorectal cancers in stages II–IV according to the TNM UICC 2010 method (based on the oncologist diagnosis) [15]; (2) patients with cachexia according to the Global Leadership Initiative on Malnutrition (GLIM) criteria [16]; (3) successful qualification to first-line radiotherapy or chemotherapy according to guideline [17]; (4) patients’ functional status is at least ≥70% according to Karnofsky scale [18]. The lower Karnofsky score indicates the lower chances of surviving; (5) individuals who have no contraindications for oral feeding and are able to be fed orally; (6) patients without acute uncontrolled underlying diseases such as kidney and/or liver failure; (7) patients at age 40 or older; and (8) men or women.

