### Study design

After obtaining informed written consent, all required measurements will be performed at the beginning of the study. Then, stratified block randomization will be done based on the type of cancer (colon or rectum) and BMI (≤23, > 23) using the www.randomization.com website. The statistician will fold the paper containing a randomization number and put them in the envelopes and write the code on them. The envelopes will be kept at the enrollment center. Then, for each qualified patient, the nutritionist randomly picks one of the envelopes after shuffling and allocates patients into control and intervention groups. It is not possible to blind study participants or staff in this study due to nutritional interventions. Nevertheless, the outcome assessor will be blinded to the group assignment.

Regarding colorectal cancer treatment, subjects with rectal cancer undergoing first-line radiotherapy and subjects with colon cancer undergoing first-line chemotherapy with capecitabine and oxaliplatin (CAPOX), 5-fluorouracil-leucovorin-irinotecan (FOLFIRI), 5-fluorouracil and oxaliplatin (FOLFOX), or capecitabine will be included [17]. As explained, people will be placed in separate blocks based on the type of cancer. The duration of the study for both intervention and control groups will be 8 weeks. Participants in the intervention group will receive a Mediterranean diet menu along with extra virgin olive oil, while participants in the control group will receive nutritional advice for cancer patients and dietary recommendations for weight gain. To assess participants’ adherence to the proposed diets, a 1-day food record will be used in the second, fourth, sixth, and eighth weeks of the study. Moreover, to encourage patients to follow the diet, all patients will be contacted weekly during the study. Participants will be asked to maintain their normal daily activities during the study. In addition, individuals’ physical activity will be monitored through completing a 1-day record in the second, fourth, sixth, and eighth weeks of the study. At the end of the study, all required measurements will be taken again in both groups. A Standard Protocol Items: Recommendations for Interventional Trials (SPIRIT) diagram for the trial schedule is indicated in Fig. 2.

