#### Assessment of other variables

General information about age, gender, education, economic status, medical history, medication and supplement use, and history of COVID-19 will be assessed by standard questionnaires. The quality of life of individuals will be assessed using the European Organization for Research and Treatment of Cancer quality of life questionnaire (EORTC QLQ-C30) (third edition) prepared by the European Agency for Research and Treatment of Cancer [23]. The validity and reliability of the questionnaires have already been evaluated in Iran [23]. In addition, the side effects of intervention as well as the treatment patients are taking such as diarrhea, nausea, constipation, vomiting, and appetite of patients will be assessed using the relevant items in this questionnaire. Also, the functional status of patients at the beginning and end of the study will also be assessed according to the Karnofsky scale. Participants will be asked to provide four 1-day food records throughout this trial. After providing the food records, the frequency of each food item will be converted to grams per day by considering the household measures of portion sizes. The daily energy and nutrient intake of each participant will be calculated by using Nutritionist IV software which is a modified food composition database based on the US Department of Agriculture.

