### Statistical analysis

Statistical analysis will be performed according to the intention-to-treat protocol; however, a per-protocol analysis will also be done. Thus, all randomized patients who have followed the Mediterranean diet for at least 2 weeks and who have the baseline measurements will be analyzed. With regard to missing data, the mean of each variable will be used to replace missing data. First, we will apply the Kolmogorov-Smirnov test to determine the normality of variables. In case of the non-normal distribution of a variable, a logarithmic transformation will be conducted. Independent sample’s *t*-test (or its non-parametric test Mann-Whitney *U*) will be used to compare the baseline values ​​of continuous variables between the two groups. Moreover, the chi-square test will be conducted to compare categorical variables. To examine the effect of the Mediterranean diet on the outcome variables, we will apply repeated measures ANOVA, in which the effect of time, intervention, and time*intervention interaction will be explored. In addition to the investigation of the crude means of variables in this analysis, we will compute adjusted means of outcome variables taking into account the baseline levels of the relevant variables. Changes in outcome variables will also be examined between the two groups using an analysis of covariance, in which the baseline values will be considered as covariates. Data will be analyzed using SPSS software version 26. *P*-value <0.05 will be considered as statistically significant.

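### The outcome models adjust only for baseline values, leaving out stage and Karnofsky; the planned baseline significance tests are no substitute, and a short prespecified covariate list would gain precision cheaply

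*Protocol article*

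**What the plan says.** - **Baseline comparison (Statistical analysis).** For continuous variables an independent-samples t-test or a Mann-Whitney test "will be used to compare the baseline values" between the arms. For the rest, "the chi-square test will be conducted to compare categorical variables". The general threshold is a P "value <0.05 will be considered as statistically significant".
- **Outcome models (same section).** A repeated measures ANOVA is to report "adjusted means of outcome variables taking into account the baseline levels of the relevant variables". Changes are compared "using an analysis of covariance, in which the baseline values will be considered as covariates". In context these are each outcome's own baseline; no other covariate is named.
- **Randomisation (Study design).** "stratified block randomization will be done based on the type of cancer (colon or rectum) and BMI", with BMI cut at 23.
- **Factors outside the strata.** The inclusion criteria admit stages II to IV and a Karnofsky status of at least 70%, and comment: "The lower Karnofsky score indicates the lower chances of surviving". Under Assessment of other variables, "the functional status of patients at the beginning and end of the study will also be assessed according to the Karnofsky scale". Stage must be known to establish eligibility, but that section does not list it as a recorded variable.

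**The concern.** After randomisation, any baseline difference between the arms is due to chance, so a significance test examines a hypothesis already known to be true. Its p-value says nothing useful about whether a given imbalance matters. That depends on the size of the imbalance and on how strongly the factor predicts the outcome. With 20 patients per arm, quite large imbalances are non-significant.

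The outcome models take in only the outcome's own baseline. Suppose stage or Karnofsky predicts week-8 PG-SGA beyond baseline PG-SGA. Leaving it out then widens the confidence interval in every realisation of the trial. In those realisations where the arms happen to differ, it also moves the estimate by the imbalance times the effect of the factor. Both factors are available at entry, so prespecified adjustment would deal with this without new data.

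**Working it through.** **Plan's own figure.** n = 2(z₀.₉₇₅ + z₀.₈₀)²s²/d² with s = 4.1 and d = 3.9: 2 × (1.96 + 0.842)² × 16.81/15.21 = 17.35 per arm. The article states 17. Dropout of 15% gives 17/0.85 = 20 per arm. The checks below use 20 per arm, SD 4.1 and d = 3.9.

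**Sensitivity of the baseline tests at 20 per arm.**
- Smallest significant mean difference: t(0.975, 38) × √(2/20) = 0.64 SD (0.70 SD at 17 per arm).
- Power of the t-test: 23% for a 0.4 SD difference, 34% for 0.5 SD.
- Chi-square without continuity correction: 12 v 8, p = 0.206; 13 v 7, p = 0.058; 14 v 6, p = 0.011.
- For any one continuous factor, a chance imbalance of at least 0.4 SD arises in 2[1 − Φ(0.4√10)] = 21% of trials. About 75% of those are non-significant.

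**Shift from a given stage imbalance.** Shift = difference in proportion × stage effect on week-8 PG-SGA beyond baseline. The article gives no stage effect, so 2, 3 and 4 points are assumed. A 30-point imbalance moves the estimate by 0.30 × 2, 3, 4 = 0.6, 0.9, 1.2 points, or 15%, 23%, 31% of 3.9. The unadjusted standard error is 4.1√(2/20) = 1.30 points. An imbalance of at least 30 points that chi-square misses occurs in about 4% of trials.

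**Type I error by simulation.** Assumptions: half the patients are stage IV, baseline to week-8 correlation is 0.5, and there is no diet effect. The analysis is the planned baseline-adjusted ANCOVA.

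| Trials considered | Stage effect 2 | 3 | 4 |
|---|---|---|---|
| All | 5.0% | 4.9% | 5.0% |
| Chi-square non-significant | 4.9% | 4.5% | 4.4% |
| Imbalance below 20 points | 4.4% | 3.9% | 3.4% |
| Imbalance ≥20 points (about 27% of trials) | about 7% | about 8% | about 10% |
| Imbalance ≥20 points and chi-square non-significant | 6.2% | 6.6% | 7.8% |

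With stage in the model, the rate for undetected imbalances is about 5%. At a stage effect of 1 point, the rate for imbalances of at least 20 points is already about 5% without adjustment. The last row is the relevant one, because the row above it includes imbalances that the test would flag.

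A second set-up uses a continuous factor, with partial correlation 0.2, 0.3 or 0.5 with the outcome. Among trials with a non-significant imbalance of at least 0.4 SD it gives 5.9%, 6.2% and 8.3% unadjusted, against 4.7%, 4.9% and 5.3% adjusted.

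**Precision.** Adding stage alone cuts the standard error by about 3%, 7% and 12% for effects of 2, 3 and 4 points. With stage and Karnofsky both moderately to strongly prognostic, the saving is about 4% to 19%. If both are useless, going from one covariate to three multiplies the standard error by about √[(N − 4)/(N − 6)]. That is √(36/34) = 1.03 at 40 patients and √(30/28) = 1.035 at 34.

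**The case against.** The case on the other side is substantial, and most of it stands.

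- **The analysis as planned is valid.** Baseline-adjusted ANCOVA keeps its level and is unbiased over randomisations. A reader might infer that omitting stage and Karnofsky biases the diet effect; the calculations do not support that. The excess error in badly balanced trials is offset by error below 5% in well-balanced ones.
- **The tests decide nothing.** A reader might infer that a non-significant result will be taken as proof of balance, or that significant variables will become covariates. The article says neither, and deleting the tests would change no planned estimate.
- **False alarms.** A reader might also expect the many baseline tests to produce a spurious imbalance in most trials. The article gives no count of tests, and many of the body-composition measures come from one impedance device and are related. A figure that assumes independent tests is not supported.
- **Prognostic strength is unproven.** The article links Karnofsky to survival, not to PG-SGA. PG-SGA itself scores physical function, so its baseline probably absorbs part of a Karnofsky imbalance. Nothing links stage to PG-SGA. The assumed 2 to 4 points is about half of d or more, and at 1 point there is no inflation.
- **A separate SAP could add covariates.** That is possible, so silence alone would not be a finding. But the article does name its tests and covariates, and those stated choices are what is questioned here.

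What the objection does not remove is the gain in precision from adjustment if either factor is prognostic, at a small cost if neither is.

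**Conclusion.** The point holds as a cheap improvement to a valid analysis. The baseline tests are uninformative under randomisation and insensitive at this size; removing them is a reporting correction only. The substantive part is the covariate list. Over all randomisations, type I error stays at about 5%. In trials with an undetected stage imbalance of at least 20 points it is about 6-8%, against about 5% with adjustment. This rests on an assumed stage effect of 2 to 4 PG-SGA points beyond baseline, half the patients at stage IV, and a correlation of 0.5. None of these stands in the article, and at about 1 point the inflation vanishes. Under moderate to strong effects of both factors, adjustment saves about 4% to 19% of the standard error.

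**What to change.** 1. In the Statistical analysis section, prespecify a short covariate list for the ANCOVA: the outcome's baseline value, baseline Karnofsky score and disease stage (II-III versus IV). Keep it whatever balance is observed. If the list must be kept short, consider the randomisation strata (cancer site, BMI) first, since the design already gives them a role.
2. Confirm that stage is entered as a baseline variable for every patient.
3. Present baseline characteristics by arm descriptively, without p-values. This changes no estimate.

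Enrolment began in January 2022 and is described as ongoing, so the change should be fixed and dated before data review.

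Cost: a sentence or two of text and no new data, because both factors are already determined for eligibility. Adding stage and Karnofsky uses two degrees of freedom, about 3% in standard error if neither proves prognostic. Adding the strata as well would use more, which is why the list should stay short at 34 to 40 patients.

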### Sample size calculation

The sample size required for the current study was calculated using the formula (*n* = 2 [(*z*1−*α*/2 + z1−*β*)^2^ · *s*^2^]/*d*^2^), which has been proposed for parallel clinical trials [24]. Considering the nutritional status (score obtained from the PG-SGA questionnaire) as the key variable [25], type I error of 5% (*α* = 0.05), type II error of 20% (*β* = 0.20, study power = 80%), standard deviation of PG-SGA score (*S*= 4.1), and *d* as equal to 3.9 [25], the required sample size for each group will be 17 patients. However, to ensure a sufficient sample size at the end of the study and taking into account the 15% probable dropout, 20 patients in each group will be recruited according to the inclusion criteria. Considering that the samples will be given in this project are among the patients referred to the radio-oncology clinic and introduced by the radio-oncology specialist, therefore, while ensuring the correct selection of samples based on the inclusion criteria, the number of patients is sufficient to reach the desired sample size for this research project.

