### Limitations

The most distinctive biomarker for examining adherence to the Mediterranean diet is the assessment of serum and urine hydroxytyrosol levels [34]. However, we will be unable to assess this biomarker as a measure of patients’ adherence to the Mediterranean diet due to limited funding. Therefore, we will use the average of four 24-h dietary records throughout the study to examine adherence to the prescribed diets. Although different modalities of cancer treatment may have an influence on nutritional status, we will stratify patients based on the type of treatment they receive. Moreover, it should be mentioned that blinding is impossible, and the risk of bias might be possible.

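### Randomisation is stratified by cancer site and BMI group, but the stated models carry neither factor, so some precision is forgone if the strata predict outcome beyond baseline

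*Protocol article*

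**What the plan says.** **Design.** Under Study design, the protocol article states that "stratified block randomization will be done based on the type of cancer (colon or rectum) and BMI", with BMI cut at 23, which gives four strata. In the same section treatment follows site: rectal cancer patients are on first-line radiotherapy and colon cancer patients on first-line chemotherapy. The drawing step reads "the nutritionist randomly picks one of the envelopes after shuffling". The text does not say whether the shuffling is done within a stratum.

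**Analysis.** Statistical analysis names three effect analyses:

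- a repeated measures ANOVA "in which the effect of time, intervention, and time*intervention interaction will be explored";
- adjusted means: "we will compute adjusted means of outcome variables taking into account the baseline levels of the relevant variables";
- a comparison of changes "using an analysis of covariance, in which the baseline values will be considered as covariates".

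The ANCOVA and the adjusted means therefore adjust for the baseline value, and the crude repeated measures ANOVA has no covariate. Site and BMI group appear in none of the three.

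**Prognostic value.** Limitations says that "different modalities of cancer treatment may have an influence on nutritional status" and gives stratification as the response. The document thus treats at least one stratum factor as potentially prognostic for nutritional status, the variable on which the trial is sized.

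**The concern.** Stratified blocks balance the arms on site and BMI group, so differences between strata largely drop out of the treatment comparison. A model without the strata still counts those differences as residual noise. Its standard error then overstates the real uncertainty, its test rejects too rarely under the null, and its power is lower than the same data could give.

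The baseline covariate removes part of this variation but need not remove all of it. A baseline score cannot carry differences that arise during the 8 weeks because one stratum has radiotherapy and the other chemotherapy. In a trial of 40 patients, sized for 17 evaluable per arm, a few points of power are worth having when the variables are already in hand.

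**Working it through.** **1. The plan's own figure.** Inputs from Sample size calculation: two-sided α 0.05, power 80%, SD 4.1, difference 3.9.

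n = 2 × (1.960 + 0.842)² × 4.1² / 3.9² = 2 × 7.849 × 16.81 / 15.21 = 17.35 per arm.

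The stated 17 is this figure rounded down; rounded up it is 18. Then 17 / 0.85 = 20, as stated. The formula has no covariate term, so the 80% relies on neither baseline nor strata.

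**2. Expected size of the effect.** Let R² be the share of residual variance, after baseline, that the strata explain. With balance kept, omitting the strata inflates the model standard error by about 1/√(1 − R²):

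- R² 0.10: 1.054
- R² 0.20: 1.118
- R² 0.30: 1.195

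The document gives no R², so it is ranged.

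**3. Simulation of the planned ANCOVA, balance kept.** 17 per arm, SD 4.1, difference 3.9, four roughly equal strata, permuted blocks of 4 within stratum, 6,000 runs per setting, baseline–outcome correlation assumed 0.5. Each cell shows baseline only → baseline + site + BMI group.

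| R² | Mean SE | Type I error | Power |
|---|---|---|---|
| 0 | 1.231 → 1.235 | 5.0% → 4.7% | 86.8% → 86.3% |
| 0.05 | 1.233 → 1.206 | 4.3% → 4.8% | 87.3% → 87.9% |
| 0.10 | 1.233 → 1.171 | 4.3% → 5.2% | 86.6% → 88.6% |
| 0.20 | 1.233 → 1.103 | 3.3% → 5.1% | 88.6% → 92.6% |
| 0.30 | 1.237 → 1.031 | 2.2% → 5.0% | 89.1% → 95.4% |

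The SE ratios agree with step 2: 1.233/1.171 = 1.05, 1.233/1.103 = 1.12, 1.237/1.031 = 1.20. At R² 0.10, 0.20 and 0.30 the power gains are 2.0, 4.0 and 6.3 points. With a baseline correlation of 0, power moves from 76.2% to 78.6%, 77.8% to 83.6% and 78.4% to 88.3%.

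**4. Strata that shift baseline and follow-up equally.** 40 patients, four strata of 10 split 5:5, 8,000 runs, within-stratum correlation 0.5, effect 0.9 SD. Here the share is of total variance.

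| Share | SE | Power |
|---|---|---|
| 0.10 | 0.266 → 0.262 | 90.9% → 91.1% |
| 0.20 | 0.255 → 0.247 | 93.4% → 94.1% |
| 0.30 | 0.241 → 0.231 | 95.7% → 96.5% |

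The SE excess is about 2% to 4%, and type I error without the strata is about 4.5%. A repeat run agreed within simulation error, so the gain is about 1 point or less. At correlation 0.7 it is 0.1 point or less, and at 0.9 there is none.

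**5. Envelopes shuffled in one pool.** Same inputs as step 3, but simple 17:17 allocation and baseline correlation 0. The baseline-only type I error is 5.1% to 5.2%, so that standard error is valid. Adding the factors changes power as follows:

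- R² 0: 76.0% → 72.7%
- R² 0.10: 75.8% → 76.6%
- R² 0.20: 74.2% → 81.1%

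**The case against.** **The loss may be negligible.** The document gives no variance share. Where the baseline value already carries the stratum difference, little is left to gain. Fat-free mass is the clearest case: BMI group is closely tied to it, but baseline fat-free mass is already the covariate for that outcome. This stands, and it makes the point one of modest efficiency. It is weaker for site, because the treatment that goes with site acts during follow-up.

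**The article is condensed.** It does not say that baseline values are the only covariates, and an unseen analysis plan may list more. That is fair. The article does, however, name its models and their terms, and that set does not match the randomisation. If the full plan already includes the strata, the article only needs to be aligned with it.

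**Stronger readings that a reader might infer:**

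- *The standard errors are simply too large.* This follows only if the strata are prognostic beyond baseline and balance is kept. If envelopes are shuffled in one pool, the baseline-only standard error is valid.
- *The comparison is confounded by site and treatment.* If shuffling loses the balance, what results is chance imbalance under random allocation. The standard error already allows for it, and it is not bias. This harm and an overstated standard error also need opposite premises.
- *The planned power is not met, or false positives rise.* The 80% comes from a formula without covariates, so the omission takes nothing from it, and the error is in the conservative direction.
- *The loss can be read from a plain two-sample comparison.* With 40 patients and SD 1 that standard error is 2/√40 = 0.316, which has no baseline term. Shares of total variance in that setting overstate what remains after baseline adjustment.

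**Conclusion.** The mismatch between design and analysis is real, and its consequence is conditional. If site and BMI group explain 10% to 30% of the variance left after baseline, and the stratified balance is kept, the stated ANCOVA overstates its standard error by about 5% to 20%. It tests at about 4% down to 2% rather than 5%, and forgoes about 2 to 6 points of power at a baseline correlation of 0.5. If the strata shift baseline and follow-up alike, the loss is about 1 point or less; if they are not prognostic, nothing is lost.

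These sizes rest on assumed variance shares, an assumed baseline correlation and roughly equal strata. The Limitations section supports the direction for treatment modality, and hence for site, but not any particular size. Neither validity nor the stated sample size is threatened. This is an inexpensive improvement worth making.

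**What to change.** Add cancer site (colon/rectum) and BMI group (≤23/>23) as fixed factors, alongside the baseline value, in the ANCOVA for each outcome. Specify this before outcome data are analysed, so that the choice cannot look data-driven; Trial status reports enrolment as ongoing. State in Study design whether envelopes are drawn within stratum, because that decides whether the baseline-only standard error would be overstated or valid.

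The cost is two model terms (2 degrees of freedom) and no new data, since both variables are needed at randomisation. If the strata turn out not to be prognostic, the price is about half a point of power with balance kept (86.8% to 86.3%). With one shuffled pool it is about 3 points (76.0% to 72.7% at baseline correlation 0), because chance imbalance then has to be adjusted for. In that one-pool case adjustment roughly breaks even at R² 0.10 and gains about 7 points at 0.20 (74.2% to 81.1%).
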